### Criteria for discontinuing or modifying allocated interventions

Participants in both groups have the ability to pause, stop and restart the messages throughout by sending an instruction to the text system, for example, ‘STOP’, ‘START’. Researchers ask women choosing to discontinue the messages to provide any reason for doing so, to inform the process evaluation. Participants discontinuing messages remain in the trial unless they formally withdraw from the trial assessments.

### Strategies to improve adherence to interventions

Text message delivery is fully automated and centrally delivered via the LSHTM system which is intended to ensure treatment fidelity. Regular monitoring of the text message system is completed by the system developer and trial team members (Chief Investigator (CI) and clerical officer) to check the content of sent and received messages (eg, ensure web links are working, review spontaneous participant responses). Intervention engagement is assessed via text messages received from participants in response to the weekly weight prompt and the replies to bidirectional messages as described in the ‘Active control’ section, self-report items in questionnaires at 6, 12 and 24 months and qualitative interviews at 6 and 12 months.

### Relevant concomitant care permitted or prohibited during the trial

Women who become pregnant during the trial will be excluded, as text message content has not been designed for pregnancy and primary outcome data (weight) can only be collected from women who are not pregnant. This is a self-directed intervention and women are permitted to access any other weight-loss services via NHS, voluntary or private sector pathways. Details of engagement with other services are captured at each data collection time point. Any weight loss surgery undergone by participants during the trial, and prescribed or over-the-counter medications that may affect weight, are documented at 6, 12 and 24 months to assess the impact on trial outcomes.

### Outcomes

Trial outcomes, measures and the assessment schedule at 0, 6, 12 and 24 months are outlined in table 1.

**Table 1 T1:** Supporting MumS trial assessments

Outcome collected	Measure/equipment used	Time point (month)			
		0	6	12	24
Anthropometric measures and demographics** *** **					
Height (m)	Portable standing stadiometer (Seca 213, Birmingham, UK)	✓			
Body weight (kg) (primary endpoint)	Calibrated scales (Seca 875, Birmingham, UK)	✓	✓	✓	✓
Waist circumference (cm)	Tape measure (Seca 201, Birmingham, UK)	✓	✓	✓	✓
Demographic characteristics†	Trial-specific questions	✓			
Acceptability outcomes					
Satisfaction with text messages‡	Trial-specific questions		✓	✓	
Acceptability of intervention, active control and study methods‡	Trial-specific questions			✓	
Longer-term use of text messages‡	Trial-specific questions				✓
Qualitative interviews	–		✓	✓	
Interviews with stakeholders	–				✓
Economic evaluation—within-trial health and social care cost data‡					
Health service resources use	Questions on health resource usage	✓	✓	✓	✓
Medication usage	Questions on over-the-counter medications	✓	✓	✓	✓
Healthy behaviour-related costs	Questions on personal expenditure	✓	✓	✓	✓
Exercise-related costs	Questions on costs of exercise	✓	✓	✓	✓
Food and drink costs	Questions on weekly cost of groceries, alcohol and smoking products	✓	✓	✓	✓
Employment status	Trial-specific questions	✓	✓	✓	✓
Health-related quality of life	EuroQol 5 Dimension 5 Level 72	✓	✓	✓	✓
Capability well-being	ICEpop CAPability measure Adults^73^	✓	✓	✓	✓
Secondary outcome measures‡					
Dietary intake	Fat and fibre barometer^74^	✓	✓	✓	✓
Sugar intake	Trial-specific questions	✓	✓	✓	✓
Alcohol consumption	Trial-specific questions	✓	✓	✓	✓
Physical activity	International Physical Activity Questionnaire—Short form^75^	✓	✓	✓	✓
Infant feeding	Infant feeding survey^76^	✓	✓	✓	✓
Moderators of intervention effect‡					
Mental health—depression	Edinburgh Postnatal Depression Scale^77^	✓	✓	✓	✓
Mental health—anxiety	Generalised Anxiety Disorder-7^78^	✓	✓	✓	✓
Mother and child relationship	MaMB/MaMC^51^ and Mothers Object Relations Scale (Baby/Child)^79^	✓	✓	✓	✓
Sleep	Pittsburgh Sleep Quality Index^80^	✓	✓	✓	✓
Confidence/importance/desire for weight loss and maintenance	Trial-specific questions	✓	✓	✓	✓
Mediators of intervention effect‡					
Intention and self-efficacy for diet and physical activity	Health Action Process Approach including action and coping planning and self-efficacy^81 82^	✓	✓	✓	✓
Habit behaviour	Self-report behavioural automaticity index^83^	✓	✓	✓	✓
Self-regulation of eating behaviour	Self-regulation of eating behaviour questionnaire^84^	✓	✓	✓	✓
Weight self-monitoring	Trial-specific questions	✓	✓	✓	✓
Diet and exercise monitoring	Trial-specific questions	✓	✓	✓	✓
Goal-setting for diet and exercise	Trial-specific questions	✓	✓	✓	✓
Weight loss motivation	Motivation for weight loss scale^85^	✓	✓	✓	✓
Taking part in other weight loss programme	Trial-specific questions	✓	✓	✓	✓
Social support	Social support for eating and exercise^86^ plus general social support (Born in Bradford trial-specific questions)	✓	✓	✓	✓
Self-esteem	Rosenberg Self-Esteem Scale^87^	✓	✓	✓	✓

*Recorded in case report form.

†Date of birth, where they heard about the trial, NHS number, ethnicity, income, postcode, employment, education, relationship status, weeks postpartum at trial entry, parity, medical information (disability status, medication use), infant feeding, weight history, smoking status, alcohol intake, technology usage.

‡Recorded in participant self-reported questionnaires.

MaMB/MaMC, Me and My Baby/Me and My Child; NHS, National Health Service.

Primary outcome: Between-group difference in mean weight change (kg) from baseline to 12 months.Secondary outcomes: Between-groups difference in mean weight change (kg) from baseline to 24 months and between-groups differences in mean waist circumference (cm), mean BMI (kg/m^2^), in the proportions of women gaining a substantial amount of weight (>5 kg), dietary intake (Fat and Fibre Barometer plus questions on sugar intake), physical activity (International Physical Activity Questionnaire-Short form) and infant feeding practices (Infant Feeding Survey), by the 12 and 24 months follow-up time points, respectively.Health economic outcomes: NHS resource use and personal expenditure (general practitioner (GP) usage, hospitalisations, prescribed and over-the-counter medications, lifestyle products and services, expenditure on food and drink, alcohol and smoking products); health-related quality of life (EuroQol 5 Dimension 5 Level with visual analogue scale) and Capability (ICEpop CAPability measure Adults).Process evaluation: To explore participants’ experiences and interactions with the intervention by site, ethnicity and SES, including evaluating dose (number of women who choose to receive all text messages and those who pause or stop the messages), engagement with the intervention (text message responses and qualitative data), reach (trial records of recruitment, loss to follow-up and withdrawal) and acceptability (participants’ satisfaction ratings and qualitative data).Exploratory outcomes: Moderator and mediator analysis (table 1).Qualitative substudy: Telephone interviews with a purposive sample of participants at six and 12 months to understand the experiences of women receiving the intervention and active control text messages and the contextual factors related to engagement including postnatal mental health, to inform trial and process evaluation outcomes.Stakeholder consultation: If the intervention is shown to be effective at 12 months, stakeholder interviews will be conducted to explore factors relevant to intervention scalability and implementation, including any further work needed to develop a coherent implementation model.

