**Methods and analysis:**

Two-arm, parallel-group, assessor-blind randomised controlled trial with cost-effectiveness and process evaluations. Women (n=888) with body mass index (BMI) ≥25 kg/m^2^ and within 24 months of giving birth were recruited via community and National Health Service pathways through five UK sites targeting areas of ethnic and socioeconomic diversity. Women were 1:1 randomised to the intervention or active control groups, each receiving automated text messages for 12 months. Data are collected at 0, 6, 12 and 24 months. The primary outcome is weight change at 12 months from baseline, compared between groups. Secondary outcomes include weight change (24 months) and waist circumference (cm), proportional weight gain (>5 kg), BMI (kg/m^2^), dietary intake, physical activity, infant feeding and mental health (6, 12 and 24 months, respectively). Economic evaluation examines health service usage and personal expenditure, health-related quality of life and capability well-being to assess cost-effectiveness over the trial and modelled lifetime. Cost–utility analysis examines cost per quality-adjusted life-years gained over 24 months. Mixed-method process evaluation explores participants’ experiences and contextual factors impacting outcomes and implementation. Stakeholder interviews examine scale-up and implementation.

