### Eligibility criteria

Women (in accordance with the NICE Postnatal care guideline NG1941, the term ‘woman’ used in this trial includes people who do not identify as women but who are pregnant or have given birth) are eligible to participate in the trial if they are aged over 18 years, have a BMI of ≥25 kg/m^2^ and have had a baby within the last 2 years.

Women are excluded if their baby is less than 6 weeks old, if they have no access to a mobile phone to allow them to receive personal text messages or if they have insufficient English language to understand short written messages, if they have had or plan to have any type of bariatric surgery, if they report having ever received a diagnosis of anorexia nervosa or bulimia from a doctor, or, if they are on a specialist diet and receiving dietetic care. Women are excluded if they are participating in any other weight management research study/programme currently or in the previous 3 months. Women are not eligible if they are pregnant and any consented participant becoming pregnant during the trial is excluded, as the intervention has not been designed for use in pregnancy.

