##### Why: theory and components

The intervention is based on the Health Action Process Approach and a systematic review of over 100 behavioural theories which synthesised theoretical explanations for maintenance of behaviour change.^54^ The intervention encourages a self-guided approach to weight-related behaviour change, as supported by the literature.^55–58^ The intervention focuses on dietary intake and physical activity to address energy balance-related behaviour, with embedded evidence-based BCTs specifically linked to the relevant phases and psychological processes of behaviour change alongside consideration of barriers for this population.^27^

The messages adopt a friendly tone including humour to foster engagement and provide information, practical tips and advice including quotes from other mothers. They signpost to external resources and provide encouragement and motivation, discourage guilt and promote self-reflection. A core library of text messages (n=353) to be delivered by the automated system was created. These include a weekly text message asking women to self-weigh and report their weight (n=50) and bidirectional messages to encourage engagement, self-monitoring, relapse prevention and to provide feedback, as follows: (1) ‘yes/no’ questions (n=36) which trigger an automated response to the participant based on their reply, (2) trigger words (‘slip-up’, ‘crave’, ‘bad day’ or ‘tired’) which can be texted by women at any time to prompt a reply designed to address these barriers and prevent relapses and (3) during months 7–12 when the focus shifts to maintenance strategies, the weekly text message asking women to report their weight asks them to add the word ‘up’ or ‘down’ or ‘same’ in relation to how their weight compares with the week prior. These keywords trigger an automated response. Responses for bidirectional messages are sent from preloaded message banks and are not individually scripted or tailored.

Women can also opt-in to receive messages related to weight management when breastfeeding (n=10) or stopping smoking (n=15). These messages are intended to alleviate participant concerns in relation to weight management while breast feeding and to address vulnerabilities around weight gain during smoking cessation.

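### Infant feeding is listed for comparison only by 12 and 24 months, when every child is past 12 months of age; the 6-month visit is left out and no account of baseline feeding or child age is stated, so the estimate is late and diluted

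*Protocol article*

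**What the plan says.** **Time points.** The Outcomes section lists between-group differences in "infant feeding practices (Infant Feeding Survey), by the 12 and 24 months follow-up time points, respectively". The Abstract (Methods and analysis) gives a different schedule for the same outcome: "dietary intake, physical activity, infant feeding and mental health (6, 12 and 24 months, respectively". Table 1 collects the Infant Feeding Survey at 0, 6, 12 and 24 months.

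**Child age.** Under Eligibility criteria, "Women are excluded if their baby is less than 6 weeks old", and women must "have had a baby within the last 2 years". The same section adds that "any consented participant becoming pregnant during the trial is excluded", so no younger child joins during follow-up.

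**Analysis.** Under Secondary outcome analysis, binary outcomes are to be analysed by logistic regression adjusted for site, recruitment method and ethnicity. Similar analyses are foreseen at other time points. Secondary analyses are declared exploratory, with the focus on estimates and 95% confidence intervals. Weeks post partum at baseline is a prespecified subgroup variable. The article does not say which variable is taken from the survey, and it states no restriction to women for whom infant feeding was still open at entry.

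**Link to the intervention.** Women may opt in to 10 messages on weight management when breastfeeding. The article says of the opt-in messages: "These messages are intended to alleviate participant concerns in relation to weight management while breast feeding".

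**The concern.** An arm comparison of infant feeding is most informative while feeding practice is still changing and while the messages are being sent. The Outcomes section places it at the end of the messages and again a year later, when no child is under 12 months. It omits the one follow-up visit at which some still are.

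As far as the article states, the comparison also pools women who were feeding a young baby at entry with women whose child was nearly two. If the measure is cumulative feeding in the first year, it was already settled before the first message for every child past 12 months at randomisation. If the measure is current feeding, women no longer breastfeeding at entry are unlikely to contribute to a difference.

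Either way, an effect among the women who could respond is averaged over many who could not. A null estimate would then not distinguish no effect from an effect that was missed.

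**Working it through.** **The plan's own figure.** No power or sample size is given for infant feeding. The primary-outcome figure, used below only for the number of completers, reproduces:
- n per group = 2 × (1.96 + 1.28)² × 7.5² / 2² ≈ 296.
- With 297 per group the power is 0.901, in line with the stated figure of over 90%.

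**Step 1: child age at each visit.** Age at visit = age at entry + follow-up time. Entry limits are 6 weeks (42 / 30.44 = 1.38 months) and 24 months.

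| Visit | Youngest (months) | Oldest (months) |
|---|---|---|
| Baseline | 1.4 | 24 |
| 6 months | 7.4 | 30 |
| 12 months | 13.4 | 36 |
| 24 months | 25.4 | 48 |

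A visit at the early edge of the ±2-week window takes 0.46 months off, so the youngest child is 12.9 months at the 12-month visit and 24.9 months at the 24-month visit. None is under 12 months at either.

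**Step 2: share of children under 12 months.** The article gives no distribution of entry ages, so this is an assumption with a range. Let u = (x − 1.38) / (24 − 1.38), where x is an age at entry.
- Under 12 months at entry, uniform: (12 − 1.38) / 22.62 = 46.9%. Hence 53.1% were already 12 months or older at randomisation.
- Under 12 months at the 6-month visit (under 6 months at entry), uniform: (6 − 1.38) / 22.62 = 20.4%.
- Entry skewed to young babies (cumulative share 1 − (1 − u)²): 28% past 12 months at randomisation; 37% under 12 months at the 6-month visit.
- Entry skewed to older children (cumulative share u²): 78% and 4%.

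**Step 3: size of the dilution.** Assume that 30% of women breastfeed at entry (range 15 to 50%) and that only they can be affected. Neither assumption comes from the article.
- A 10-point difference among them appears in all women as 0.30 × 10 = 3 points (range 1.5 to 5).
- With 297 per arm and an assumed overall rate of 10%, the 95% half-width is 1.96 × √(2 × 0.10 × 0.90 / 297) = 4.8 points.

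**Step 4: can the all-women comparison detect anything?** With 297 per arm and illustrative 12-month rates, power is 93% for 20% v 10%, 76% for 15% v 8%, 64% for 10% v 5% and 51% for 5% v 2%. Each of these roughly halves the rate, or more, over all women. If only 30% are at risk, 20% v 10% needs a difference of 10 / 0.30 = 33 points among them.

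**Step 5: what the subset buys in precision.** Thirty per cent of 297 is about 89 per arm. A 10% overall rate confined to them is 0.10 / 0.30 = 33%. The half-width is 1.96 × √(2 × 0.333 × 0.667 / 89) ≈ 13.8 points. The ratio of effect to half-width is 10 / 13.8 = 0.72 in the subset and 3 / 4.8 = 0.63 in all women.

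**The case against.** The strongest reply is that most of the remedy is already in the plan. The Abstract names 6 months, Table 1 collects the survey then, and the secondary analysis section allows for other time points. The mismatch also covers waist circumference, BMI, diet and physical activity, which share the same sentence. The survey variable is not shown, and it may be a duration or time of stopping. Its definition, the women analysed and the covariates may properly sit in the SAP.

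Much of this stands. The 6-month comparison is not ruled out, and silence about the survey variable is no fault in an article. What remains is that two sections of the same document give different time points. For infant feeding, unlike the other outcomes in that sentence, the omitted visit is the only one that catches any child under 12 months. The adjustment set that the article does state for binary outcomes leaves out baseline feeding and child age.

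A reader might go further and infer that the outcome cannot show an effect or a harm, or that it is at its floor by 12 months. The documents do not support this. They give no feeding rate, breastfeeding can continue past 12 months, *by* 12 months may mean cumulative practice, and the illustrations in Step 4 reach up to 93% power. Nor do they present reduced breastfeeding as an anticipated harm. The opt-in messages answer participants' concerns, and infant feeding is nowhere called a safety outcome.

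It is also fair to say that the subset analysis gains little precision: on the assumed figures neither comparison would detect a 10-point effect among the women at risk.

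**Conclusion.** The point holds in a limited form. The child ages follow from the entry limits alone: none is under 12 months at either time listed in the Outcomes section. The 20% under 12 months at the 6-month visit (4 to 37%) and the 53% past 12 months at randomisation (28 to 78%) rest on assumed entry-age distributions. Taking under 12 months as the marker of infancy is a choice made here; the article itself speaks of babies up to 36 months when describing the control messages.

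The dilution from 10 points to 3 rests on an assumed 30% breastfeeding at entry. The estimate is late, diluted and hard to interpret if null, though not incapable of showing a difference. Severity is minor.

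**What to change.** - Reconcile the Abstract and the Outcomes section, and list 6 months as the main time point for infant feeding.
- Adjust this outcome for feeding status at baseline and weeks post partum, in addition to site, recruitment method and ethnicity.
- Report the comparison among women breastfeeding at baseline (still breastfeeding at 6 months, and duration by 12 months) alongside the all-women result. The subset is defined before randomisation, so the arms remain comparable.
- Label the 24-month comparison descriptive.

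The cost is wording in the protocol and SAP. Baseline feeding, weeks post partum and the 6-month survey are already collected. The subset interval is wider on its own scale (about 14 points against 4.8 on the assumptions above), so the gain is a better-targeted estimate more than a more precise one. If baseline status predicts later breastfeeding almost perfectly, the all-women logistic model may not fit cleanly, and the SAP should say how that will be handled.

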### Participant timeline

The trial flow chart includes the participant timeline for the RCT (figure 1).

**Figure 1 F1:**
[figure not shown]
Supporting MumS trial flow chart. GP, general practitioner; PPI, personal and public involvement.

### Sample size

The target sample size is 888 women over 12 months, with site-specific targets across the five geographical areas (London and Bradford, n=189, respectively; Belfast, Stirling and Cardiff, n=170, respectively). Pregnancy-related withdrawals are not replaced unless the loss to follow-up (12%) or pregnancy rates (15%) observed in the pilot RCT^27^ are exceeded by the 6-month time point, which is monitored during project management team (PMT) meetings.

#### Sample size calculation

The pilot trial showed a mean weight loss of 1.75 kg in the intervention group compared with a mean gain of 0.19 kg in the active control group between baseline and 12 months, equating to a between-groups difference in mean weight change, adjusted for baseline, of −1.67 kg (95% confidence interval −4.88 to 1.55)).^27^ Based on pilot data for the active control group and a standard deviation of 7.5 kg, 594 completing participants (297 per group) are required to give the trial over 90% power to detect a statistically significant difference of 2 kg in mean weight change from baseline, at the 5% level, between groups. A mean difference of 2 kg is accepted as being associated with metabolic health benefits and is often used to power weight loss studies.^58^

We observed a 15% pregnancy drop-out rate in the pilot study, based on a 99% white ethnicity population.^27^ Data from South Asian women in the Born in Bradford’s Better Start (BiBBS) cohort^61^ indicate that pregnancy drop-out rates could be higher in more ethnically diverse samples, around 22%. To have 119 participants completing per site and accounting for a loss to follow-up rate of 15% and higher anticipated pregnancy exclusion rates in areas with greater ethnic diversity, the following site-specific sample sizes were calculated: (1) Belfast, Stirling and Cardiff; 15% pregnancy rate +15% loss to follow-up=170 women, (2) Bradford and London; 22% pregnancy rate +15% loss to follow-up=189 women. Therefore, the total sample size for the trial is 888 women (444 per group).

### Recruitment

Based on successful pilot study recruitment processes,^27^ trial information is disseminated via community settings likely to be attended by mothers of young children (eg, parent and toddler groups, libraries, breastfeeding support groups), social media and through contacts with healthcare professionals and GP practices, including both routine appointments and contacting potentially eligible women identified using patient database searches. A range of recruitment pathways are used to target ethnically and socioeconomically diverse populations.

In Bradford, principal trial recruitment is through BiBBS, an existing birth cohort study, with trial information disseminated to participants who previously consented to be informed of other relevant research studies.

